## 2 Methods and analysis

### 2.1 Study design and settings

The FREEDOME study (*E*ff*icacité d'un programme mixte de*
ré*habilitation n*e*uropsychologique en*
d*istanciel chez*
d*es patients porteurs d'un gli*ome
*diffus de grade 2 ou 3: essai randomisé contrôlé*, Efficacy of a hybrid neuropsychological telerehabilitation intervention on cognitive complaints in patients with LrGG after therapy) (NCT06468176) is an ongoing, prospective, open-label, multicenter, randomized controlled trial carried out in France. Patient recruitment is open since June 2024. The study is expected to last 42 months in total: 24-month enrollment period and 18-month follow-up phase. Patient will be included through a two-step process that includes screening and inclusion visits. Eligible patients who consent to participate will sign a written informed consent (Supplementary material) before enrollment. Patients will be randomly allocated to the control arm (standard care) or the intervention arm (FREEDOME program) (1:2 ratio). Figure 1 shows the study timeline and Figure 2 the study flowchart. Table 1 presents the data collection schedule. This study follows the Standard Protocol Items: Recommendations for Interventional Trials (SPIRIT) checklist to ensure the quality of the study protocol.

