**Figure 2 F2:**
[figure not shown]
Flow diagram of the study FREEDOME. ^1^Expected number of patients. ^2^Chemotherapy or radiotherapy. ^3^Performed by a trained onco-neuro-psychologist (max 1 session/week for 15 weeks). ^4^Four-month program (Insight from Posit Science BrainHQ, San Francisco, California, 357 USA). FACT-Cog, Functional Assessment of Cancer Therapy-Cognitive Scale; PCI, Perceived Cognitive Impairment sub-score; HADS, Hospital Anxiety and Depression Scale.

**Table 1 T1:** Detailed data collection schedule.

**Data collected**	**Screening inclusion**	**Intervention**	**EOI visit (T1)**	**FU visit (T1^′^)**	**FU visit (T2)**	**EOS visit (T2^′^)**
	**D**_−15_ **to D**_−1_	**W1–15**	**M4** ±**2W**	**M6** ±**2W**	**M12** ±**2W**	**M18** ±**2W**
Eligibility criteria	✓					
Consent form signature	✓					
Randomization	✓					
Cognitive complaints (patient- ± caregiver-rated FACT-Cog, PRMQ)	✓		✓	✓	✓	✓
Psychological functioning (patient- ± caregiver-rated HADS, BDI-II, STAI-Y, BITe)	✓		✓	✓	✓	✓
Quality of life (EORTC QLQ-C30, BN20)	✓		✓	✓	✓	✓
Fatigue (MFI-20, ISI)	✓		✓	✓	✓	✓
Neurocognitive functioning (MoCA, WAIS-IV subtests, HVLT, SENTB, RMET)	✓		✓		✓	
CBT by videoconference (at least 3 sessions, maximum 1 session/week)		✓^a^				
BrainHQ program (4 × 40-min session/week)		✓^a^				

BDI-II, Beck Depression Inventory-II; BITe, Brief Irritability Test; CBT, Cognitive Behavioral Therapy; EORTC QLQ-C30 and BN20, European Organization for Research and Treatment of Cancer Core 30 and Brain-20; FACT-Cog, Functional Assessment of Cancer Therapy-Cognitive questionnaire; HADS, Hospital Anxiety and Depression Scale; HVLT, Hopkins Verbal Learning Test; ISI, Insomnia Severity Index; MoCA, Montreal Cognitive Assessment; PRMQ, Prospective and Retrospective Memory Questionnaire; RMET, Reading the Mind in the Eyes Test; SENTB, Standard Executive Neuropsychological Test Battery; STAI-Y, State-Trait Anxiety Inventory-Y; WAIS-IV, Wechsler Adult Intelligence Scale, Fourth Edition, subtests Coding and Symbol Search.

D, day; W, week; FU, follow-up, EOI, end of intervention, EOS, end of study.

^a^Experimental group only.

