### 2.4 Eligibility criteria

#### 2.4.1 Inclusion criteria

Age ≥ 18 years.Histomolecular diagnosis of LrGG according to the 2021 WHO classification, regardless of prior oncological treatments.Eastern cooperative oncology group performance status (ECOG-PS) score ≤ 2.Neurosurgical resection (excluding biopsy) performed ≥12 months before inclusion.Cancer treatment (chemotherapy or radiation therapy) completed at least 6 months before inclusion.Cognitive complaints defined at least as “*Quite*” on items 20 and/or 25 of the EORTC QLQ-C30 questionnaire (i.e., “Cognitive Functioning” subscale score ≤ 66.67).Patient fluent in French.Patient covered by the French Social Security system.Regular use of digital tools and internet access.Signed informed consent.

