### 2.7 Intervention protocol

At the screening visit, the investigator (a neuro-oncologist or an onco-neuro-psychologist) will confirm the patient's eligibility criteria and collect the informed consent form.

At the inclusion telehealth session, the onco-neuro-psychologist will collect demographic data, symptoms, rehabilitation status, concomitant treatments, disease history, prior oncological treatments, tumor laterality and eloquence, seizure frequency, time since last treatment, and scores from self-rated questionnaires and from clinician-rated neurocognitive tests. A comprehensive neuropsychological assessment will be performed, focusing on cognitive complaints, psychopathological states, HRQoL, fatigue, and objective neurocognitive functioning. The patient will then be randomized.

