- the FACT-Cog PCI scores will be compared between arms and time points using a similar method. A 5% significance threshold will be applied with adjustments for multiple comparisons to control the alpha risk using the Benjamini–Hochberg method (Benjamini and Hochberg, 1995). All exploratory analyses will be performed without adjustment.- Partial correlations between the FACT-Cog or PRMQ subscale score and key cognitive domains will be evaluated using Spearman or Kendall Tau correlation coefficients, adjusted for distress (HADS) and fatigue (MFI-20, ISI). Each neuropsychological threshold will be defined according to the test guideline and taking into account many variables, such as age, sex and/or socio-cultural level.- Other questionnaire scores will be compared between arms with the Student's *t*-test or Wilcoxon/Mann-Whitney rank-sum test. An ANOVA or ANCOVA model will be used to adjust for potential confounders.

Within each arm, score differences (HADS, PRMQ, BDI-II, STAI-Y, BITe, MFI-20, ISI, QLQ-C30, and BN20) between baseline and the subsequent timepoints will be assessed using the paired Student's *t* or Wilcoxon signed-rank test.

First, the mean score change over time will be graphically represented using the LOcally Estimated Scatterplot Smoothing method (LOESS).

Then, Linear Mixed Models (LMMs) may be used to model the score changes over time in function of the group. These LMMs will include random intercepts and slopes, assuming a linear trajectory over time. If necessary, more flexible LMMs (e.g., spline-based models) may be considered.

Although the open-label design may expose the study to attention and expectancy biases, particularly regarding self-reported outcomes, the data analysts involved in the primary outcome analysis will remain blinded to group allocation.

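### If the QLQ-C30 score that admits a patient is also the baseline, the within-arm tests of Cognitive Functioning are liable to show improvement through regression to the mean alone

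*Protocol article*

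**What the plan says.** Section 2.4.1 of the protocol article requires a minimum level of complaint on "items 20 and/or 25 of the EORTC QLQ-C30 questionnaire (i.e., “Cognitive Functioning” subscale score ≤ 66.67". A low score on this two-item subscale is therefore a condition of entry.

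Table 1 has one column before the intervention, headed as screening and inclusion together and spanning day −15 to day −1. The row that begins "Quality of life (EORTC QLQ-C30, BN20" has one tick in that column, then ticks at M4, M6, M12 and M18.

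Two other places bear on when the baseline is taken. Section 2.1 says: "Patient will be included through a two-step process that includes screening and inclusion visits". Section 2.7 says that at screening the investigator "will confirm the patient's eligibility criteria and collect the informed consent form". At the later inclusion session, before randomisation, the onco-neuro-psychologist collects a list of items that includes "time since last treatment, and scores from self-rated questionnaires and from clinician-rated neurocognitive tests". The article does not say whether the QLQ-C30 used for eligibility is carried forward or answered again.

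Section 2.13 plans paired t or signed-rank tests of "Within each arm, score differences (HADS, PRMQ, BDI-II, STAI-Y, BITe, MFI-20, ISI, QLQ-C30, and BN20) between baseline and the subsequent timepoints", so the QLQ-C30 is among the scores tested separately in each arm. It also plans between-arm tests of the same questionnaires and allows ANOVA or ANCOVA adjustment. Regression to the mean is not mentioned.

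**The concern.** A patient chosen because one measurement was low will, on average, score higher the next time even if nothing has changed, because part of the low score was chance. If that same measurement is the starting point of a paired test, the test counts this rebound as improvement. It happens in both arms and at every later visit.

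The subscale measures cognitive complaint, which is the trial's central construct, and the QLQ-C30 is a listed secondary endpoint. A significant rise from baseline in the intervention arm would be easy to read as support for the programme. The 2:1 allocation adds to this: the larger arm is more likely to reach significance from the same artefact, so a null trial can readily give a significant intervention arm beside a non-significant control arm.

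**Working it through.** **The plan's own figure.** Section 2.5 gives a difference of 6.5, SD 14, two-sided α 0.05 and 80% power; section 2.6 gives 2:1 allocation. Control n = (1.960 + 0.842)² × 14² × (1 + 1/2) / 6.5² ≈ 54.6, so 55 + 110 = 165. The stated 168 (56 + 112) has 80.5% power by the noncentral t distribution, and 187 × 0.90 = 168.3. The sample size reproduces. It matters here only because it gives the arm sizes at M4: 168 × 2/3 = 112 and 168 × 1/3 = 56.

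**Inputs for the check.**
- Selected fraction p = 0.50. Section 2.5 expects about half of screened patients to be eligible on all criteria, and the introduction reports cognitive complaints in 40–53% of a similar group.
- Test-retest correlation r between the entry score and the later score: not in the article; assumed 0.6 to 0.9.
- No true change; entry score used as baseline.
- SD of the subscale among those screened: not in the article; 25 points assumed only to convert SD units to points.

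**Formulas.** For a normal score with the lowest fraction p selected, the spurious rise in SD units is (1 − r) × φ(z_p)/p. At p = 0.50 this is (1 − r) × 0.3989/0.50 = (1 − r) × 0.798. The variance of the change among those selected is (1 − r)² × (1 − 2/π) + (1 − r²). The noncentrality of the paired t-test is rise/SD of change × √n.

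| r | Rise (SD) | Points at SD 25 | SD of change | Significant rise, n = 112 | Significant rise, n = 56 |
|---|---|---|---|---|---|
| 0.6 | 0.32 | 8.0 | 0.83 | 98% | 80% |
| 0.7 | 0.24 | 6.0 | 0.74 | 93% | 67% |
| 0.8 | 0.16 | 4.0 | 0.61 | 78% | 48% |
| 0.9 | 0.08 | 2.0 | 0.44 | 47% | 26% |

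For r = 0.8 and n = 112, for example, 0.160/0.61 × √112 ≈ 2.8, which gives 78%. A sound test would give a significant rise in 2.5% of null trials. Over the same range of r, the rise is 0.10 to 0.39 SD at p = 0.40 and 0.08 to 0.30 SD at p = 0.53.

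**Check on the real scale.** A simulation used two four-level items, with selection on at least one item at the third level or worse. With item reliability from 0.9 to 0.5, it gave spurious rises of 3.4 to 10.4 points. The within-arm test rejected in 69–99% of trials with n = 112 and 43–89% with n = 56. The between-arm test of change rejected in 4–5%, as it should.

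**The two arms side by side.** At r = 0.8, with no true effect and independent arms, a rise that is significant in the intervention arm only occurs in about 0.78 × 0.52 = 41% of trials. The reverse occurs in about 0.22 × 0.48 = 11%.

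**If the baseline is a fresh questionnaire at inclusion.** The rise becomes (r_short − r_long) × 0.798, where r_short is the correlation of the screening score with the inclusion score and r_long its correlation with the later score. With equal correlations it is zero, and in the two-item simulation the within-arm rejection rate returned to about 5%. If the correlation falls from 0.80 to 0.75 or to 0.60, the rise is 0.04 or 0.16 SD.

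**The case against.** The strongest reply is that the article nowhere says that the entry score is the baseline. The merged column of Table 1 also holds eligibility, consent and randomisation, so one tick there cannot distinguish one administration from two. Sections 2.1 and 2.7 describe two steps, with self-rated scores gathered at the second, and section 2.12 has patients introduced to the questionnaire application on inclusion. A separate baseline may already be the practice. This stands, and it makes the point conditional.

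It is also fair that the paired tests are supportive. Between-arm tests of the same scores are planned, the discussion rests the claim of impact on the randomised design, and a statistical analysis plan is still to be drafted. This limits the consequence. It does not make the paired test on this subscale interpretable if the score is reused, and the article itself commits to that test.

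A reader might infer more than the document supports, in three ways:
- That all QLQ-C30 within-arm tests are biased. Selection acts directly on the two-item Cognitive Functioning subscale only. Other scales shift only if their correlation with the entry score weakens over time: 0 to 0.12 SD in the cases tried.
- That both arms are certain to show improvement. The control arm reaches significance in only 26 to 48% of trials at r = 0.9 to 0.8.
- That the FACT-Cog PCI comparisons share the problem. PCI is not in the within-arm list, the article gives nothing from which to size such an effect, and its randomised comparison is unbiased in any case.

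**Conclusion.** The point holds conditionally and for one subscale. If the eligibility QLQ-C30 is reused as baseline, the within-arm tests of Cognitive Functioning are liable to report improvement where there is none, at many times the nominal 2.5%. The size rests on the assumed test-retest range, a selected fraction near one half, no true change and the M4 arm sizes; rates would be somewhat lower at M12 and M18, where section 2.5 expects fewer patients. If a separate QLQ-C30 is taken at inclusion and the correlation is stable, the bias disappears. The sample size, the primary endpoint and every randomised between-arm comparison are untouched. This is a limited flaw in a supportive analysis.

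**What to change.** In the statistical analysis plan:

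1. Take the Cognitive Functioning subscale out of the within-arm significance tests. Show its course in each arm descriptively, with a note that change from baseline may include regression to the mean.
2. Draw inference on this subscale only from the baseline-adjusted between-arm comparison (ANCOVA), which section 2.13 already allows.
3. State whether the QLQ-C30 is answered again at the inclusion session or the screening score is carried forward.

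The first two steps are sound under either reading of Table 1. They cost a few sentences and one within-arm p-value per visit and arm, which could not be interpreted if the entry score is the baseline. The baseline questionnaire procedure should not be changed now: recruitment has been open since June 2024, and patients enrolled before and after a change would have differently defined baselines.

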### 2.5 Sample size

To identify clinically meaningful improvements, responders will be defined as patients who show a FACT-Cog PCI score reduction of at least 6.5 points between baseline and M4. This threshold is based on previously validated minimal clinically important differences observed in patients with cancer, and estimated from the results of the TémoIN trial (NCT03257618) (Darlix et al., 2024) and the study by (Bray et al. 2017). A sample size of 168 evaluable patients is required to detect a 6.5-point mean difference in the FACT-Cog PCI score (control: 50, intervention: 56.5) with 80% power, two-sided α = 0.05, and an assumed standard deviation of 14 (Darlix et al., 2024; Bray et al., 2017). To take into account drop-outs, a conservative attrition rate of 10% was considered for this clinically stable LrGG population. This rate is consistent with attrition benchmarks in glioma trials, but it is likely to overestimate losses in cohorts of patients with clinically stable LrGG that are generally characterized by higher retention. Participation burden (many questionnaires at multiple time points) was also taken into account.

Therefore, 187 patients will be enrolled (187 × 0.90 = 168 patients evaluable at M4 for the primary endpoint). Based on prior observations from the TémoIN study (NCT03257618) showing that ~50% of screened patients were eligible, 374 patients will be screened over 24 months to reach the planned sample size (*n* = 187).

For the secondary endpoints, cumulative attrition is conservatively projected as follows: =10% by M6, =15% by M12, and =20% by M18. These estimates reflect modest progressive losses to follow-up, but also take into account the relative functional stability of patients with LrGG and the planned retention strategies (flexible schedule, family caregiver engagement, proactive follow-up). Sample size targets and the resulting evaluable number of patients were adjusted to align with these timepoint-specific attrition expectations, ensuring sufficient power for the primary and secondary analyses. Using these estimates, the expected number of evaluable participants at each scheduled assessment is reported in Figure 2.

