### 2.6 Randomization

Patients will be randomized in a 2:1 ratio (intervention: control) using a random block randomization method. This approach will maximize the number of patients who can benefit from the FREEDOME program. Stratification factors include:

Number of treatment lines (chemotherapy or radiotherapy, 0 vs. 1–2 vs. > 2);Baseline FACT-Cog PCI score (cognitive complaints) and HADS (distress) score (PCI score ≤ 47 and/or HADS score ≥13/42 vs. PCI score >47 and HADS score <13/42);Tumor histological grade (grade 2 vs. 3).

Investigators will register patients using the online electronic case report form (Ennov Clinical^®^).

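### The optional longitudinal model defaults to a straight line from baseline to M18 although the program ends at about M4, and the within-arm tests have unequal power under 2:1 allocation

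*Protocol article*

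**What the plan says.** All of this stands in section 2.13 (Data analysis) of the protocol article and concerns secondary endpoints.

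- **Longitudinal model.** After a LOESS plot of mean change, linear mixed models are offered as an option. Their form is then fixed: "These LMMs will include random intercepts and slopes, assuming a linear trajectory over time". The next sentence allows more flexible models such as splines if needed, without saying what would show the need.
- **Within-arm tests.** "Within each arm, score differences (HADS, PRMQ, BDI-II, STAI-Y, BITe, MFI-20, ISI, QLQ-C30, and BN20) between baseline and the subsequent timepoints will be assessed", by paired t or signed-rank test.
- **Between-arm tests.** The other questionnaire scores are also compared between arms by t or rank-sum test, with ANOVA or ANCOVA to adjust for confounders.
- **PCI beyond the primary endpoint.** "the FACT-Cog PCI scores will be compared between arms and time points using a similar method". The method just described is the t or rank-sum test with ANOVA or ANCOVA. FACT-Cog is not in the list of scores with paired tests.

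Related design facts: training runs for 15 weeks (section 2.8.2). Visits are at baseline, M4, M6, M12 and M18 (Table 1). Section 2.6 states: "Patients will be randomized in a 2:1 ratio (intervention: control) using a random block randomization method". Effects at M4, M6, M12 and M18 are stated secondary objectives (section 2.2).

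**The concern.** A straight-line arm-by-time term assumes that the difference between arms grows by the same amount each month from baseline to M18, including the 14 months after the program has ended. If the effect builds by M4 and then holds or fades, the line understates it early and either invents later growth or shows no slope at all. Durability is what the M6-M18 analyses are meant to describe. A switch to splines without a rule would be decided after the curves have been seen, and section 2.13 promises blinded analysts only for the primary outcome.

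The within-arm tests raise a separate problem. The intervention arm has twice the patients, so an identical change in both arms is more often significant there. Patients are selected for cognitive complaints (section 2.4.1), so improvement in both arms without any program effect is possible. A significant result in one arm beside a non-significant one in the other is easily read as a program effect.

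**Working it through.** **1. The plan's own figure.** Inputs from section 2.5: difference 6.5 points, and "with 80% power, two-sided α = 0.05, and an assumed standard deviation of 14"; allocation 2:1. Control n = (1 + 1/2)(1.960 + 0.842)² × 14² / 6.5² = 54.6, so 55 + 110 = 165. An exact t calculation gives 79.8% power at 55/110 and 80.5% at 56/112. The stated 168 is reproduced, and 168/0.90 = 186.7 gives the 187 enrolled. At 2:1, 168 evaluable means 112 and 56.

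**2. What a straight line would require.** A line through zero at baseline and 6.5 at M4 reaches 6.5 × 18/4 = 29.25 points at M18, about 2.1 SDs (29.25/14).

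**3. A line fitted to other shapes.** Months 0, 4, 6, 12, 18 have mean 8, deviations -8, -4, -2, 4, 10 and sum of squares 200. The profiles are assumptions; the article gives none.

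- *Plateau* (0, 6.5, 6.5, 6.5, 6.5): slope = 6.5 × (-4 - 2 + 4 + 10)/200 = 52/200 = 0.26 per month; intercept = 5.2 - 8 × 0.26 = 3.12. Fitted differences are 3.1, 4.2, 4.7, 6.2 and 7.8. The 3.1 falls at baseline, where randomisation makes the expected difference zero. The fitted change from baseline is 4 × 0.26 = 1.0 at M4 and 18 × 0.26 = 4.7 at M18; the truth is 6.5 at both.
- *Fading* (0, 6.5, 5.5, 3.5, 1.5): slope = (-26 - 11 + 14 + 15)/200 = -0.04 per month.
- *Falling linearly from 6.5 at M4 to half by M18*: slope 0.065 per month.
- *Falling linearly from 6.5 at M4 to zero by M18*: slope -0.13 per month.

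With complete data, generalised least squares under random intercepts, with or without random slopes, gave the same fitted lines as ordinary least squares. The result is therefore not an artefact of leaving out the random effects.

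For the slope test, assume visit correlation 0.5 (residual variance 98) and no random slope: SE = √[(98/200)(1/56 + 1/112)] = 0.115. The fading slope is then about 0.35 SE from zero. Power is about 9% for the half-fade and 62% for the plateau. A random-slope SD of 0.5 per month lowers these to about 7.5% and 46%.

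**4. Within-arm tests with no program effect.** Assume the same true change of 4 points in both arms. The SD of 14 is the PCI value, borrowed as a yardstick because PCI is not on the within-arm list; only the ratio 4/14 = 0.29 SD matters. SD of change = 14√[2(1 - ρ)], with ρ assumed at 0.3-0.7. Arms are independent, so P(intervention only) = power in intervention × (1 - power in control).

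| ρ | power, n = 56 | power, n = 112 | intervention only | control only |
|---|---|---|---|---|
| 0.3 | 43% | 72% | 41% | 12% |
| 0.5 | 56% | 85% | 38% | 8% |
| 0.7 | 77% | 97% | 22% | 2% |

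With a common change of 3 points, intervention only occurs in 35-40% of trials; with 5 points, 8-35%. At M18, 187 × 0.80 is about 150 patients (100 and 50). With ρ = 0.5 and 4 points, the figures are 40% and 10%. Nine instruments at four visits in two arms give at least 9 × 4 × 2 = 72 such tests.

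**The case against.** The section contains real safeguards. The mixed model is optional, follows a plot that could reveal a bend, and has a spline fallback; the statistical analysis plan, still to be drafted, may supply the rule. Between-arm comparisons with covariate adjustment are planned for the same scores, so a benefit that fades would still be estimated visit by visit. The article states no expected trajectory, so the plateau and fading shapes are assumed. All of this stands, and it confines the harm to the longitudinal model, its slope test and the way within-arm results may be read. It does not remove the point: the linear form is a stated default, not a detail left open, and the within-arm tests carry no statement that the between-arm contrast takes precedence.

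Two stronger readings are tempting and should be resisted.

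- A reader might infer that PCI will be compared across visits by unpaired tests. The text does not say so. A similar method can include ANCOVA or a paired test, and the absence of FACT-Cog from the paired list may only be terse wording. Even if unpaired tests were used, the error would be conservative: true alpha about 1.9%, 0.6% and 0.03% at correlations 0.3, 0.5 and 0.7. Power would be lost, but no false positives created.
- A reader might infer that a program effect will be claimed from within-arm p-values. Nothing in the article says that.

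**Conclusion.** The point holds for the secondary longitudinal analyses. A linear-time default suits a 15-week program with follow-up to M18 poorly. Under an assumed 6.5-point plateau it misplaces the effect (3.1 at baseline, 4.2 at M4, 7.8 at M18), and under an assumed fade its slope test has almost nothing to detect. Separately, 2:1 allocation makes the within-arm tests lopsided: about 22-41% against 2-12% under an identical 4-point change. The sizes rest on assumed profiles, common change and correlations. The direction of the lopsidedness does not; its size shrinks when the common change is large enough for both arms to be significant. The primary M4 comparison and its sample size are not affected. The wording on PCI across time points is ambiguous and no more than that.

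**What to change.** In section 2.13 and the analysis plan, replace the linear-time default with one repeated-measures mixed model per score: arm, visit as a category, arm-by-visit, baseline score, the stratification factors of section 2.6 and an unstructured covariance. Report the between-arm difference with 95% CI at M4, M6, M12 and M18 (M4 and M12 for the neurocognitive tests, which are given only then). Report within-arm changes descriptively, without p-values. The same model settles the PCI wording, because it respects the correlation within patients.

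The cost is wording only: no new data and fewer tests. The downside is a few more parameters. Four post-baseline visits need 4 × 5/2 = 10 covariance parameters, against 4 for random intercept, slope, their covariance and the residual. That is modest for about 168 patients.
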